## Abstract

**Introduction::**

Transitional drainage, which is followed by cholecystectomy plays a key role in the management of acute cholecystitis, especially in high-risk surgical patients. Endoscopic naso-gallbladder drainage (ENGBD) is an alternative to percutaneous transhepatic gallbladder drainage (PTGBD) for patients who need temporary drainage. There is a lack of prospective comparison on the relevant outcomes of the two drainage methods during the period of drainage, especially the subsequent cholecystectomy.

**Methods::**

This is a randomized controlled two-arm non-blind single center trial. Patients with acute cholecystitis undergo emergent or early cholecystectomy and need drainage will be randomly assigned to group PTGBD or ENGBD. Pain score is defined as the primary endpoint, whereas several secondary endpoints, such as the rates of technical success, clinical remission, open conversion of cholecystectomy will be determined to elucidate more detailed differences between two groups. The general feasibility, safety, and quality checks required for high-quality evidence will be adhered to.

**Discussion::**

This study would provide the first type A evidence concerning the comparison of ENGBD versus PTGBD in surgically high-risk patients with acute cholecystitis, it will be the first trial designed to determine the impact of two drainage methods on not only peri-drainage but also peri-LC.

**Trial registration::**

NCT03701464. Registered on October 10, 2018.

PTGBD has a technical success rate of nearly 97%, clinical response rates range from 56% to 100%,^[6]^ which is also associated with an overall adverse events rate as high as 14%, including bile leak peritonitis, cholecystitis, bleeding, subcapsular hematoma, pneumothorax, catheter misplacement, and inadvertent removal. Moreover, it is contraindicated in patients with large peritoneal ascites, coagulopathy, thrombocytopenia, and Chilaiditi syndrome.^[5]^ For these reasons, less-invasive forms of ENGBD that are more efficient, more safe and less painful have been developed.^[10]^ It was first proposed in 1984, but reported in 1990,^[11]^ the technical success, clinical success, post-procedure adverse events were 88.9%, 81.5%, 9.3%, respectively, according to the data provided by the only two randomized controlled studies^[9,12]^ in comparing ENGBD and EGBS. Despite such promising achievement from previous studies, the benefits of ENGBD and PTGBD on major clinical outcomes have never been compared prospectively. In particular, the effects of the two drainage method on LC remains uncertain and not only an extensive evaluation but also a retrospective study pointed out that ENGBD was more conducive to the smooth implementation of LC.^[13]^

## Methods

2

### Primary objective

2.1

The primary objective of the study is to determine the clinical pain remission of ENGBD versus PTGBD in patients requiring temporary gallbladder drainage, our hypothesis is that in comparison with standard PTGBD, ENGBD could not only relieve the pain symptoms associated with acute cholecystitis itself, but also relatively alleviate the severe pain caused by drainage.

### Secondary objectives

2.2

The study will also compare ENGBD and PTGBD on clinical outcomes of drainage and the difficulties of cholecystectomy in surgically high-risk patients with acute cholecystitis, especially drainage success rate, clinical remission, and adverse events. Also, their impacts on cholecystectomy will be focused and targeted, including difficulty grading of cholecystectomy, cholecystectomy duration, pathology, and so on.

### Trial design

2.3

The trial is an investigator-initiated, parallel group, single-center, randomized controlled, with the allocation ration of 1:1, non-blind trial; however, the statistician would not know the grouping.

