### Allocation sequence generation and randomization

2.12

The randomization numbers were generated by statistician using computer program with 1:1 allocation, stored and encoded 20 sealed, opaque envelopes independently. When a participant meets inclusion and inclusion criteria, two volunteers first record the name and the code of the next unopened envelope, then open the envelope and sign their names. At last, the treatment assignment would be sent to the attending physicians, which could get only one allocation at a time after all pre-drainage preparations were completed, including the evaluation of patients and informed consent of participants.

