### Blinding

2.13

This is an open-label, unblinded trial for patients and physicians because of the nature of the intervention (position and shape of drainage tube). However, the investigator of collecting secondary outcomes, the assessor of clinical and biological data in charge of statistical analyses and outcome assessment will be masked as to the subjects assigned group.

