#### Collection, management

2.14.1

All data are prospectively collected and managed by the well-trained research volunteers.

The baseline data would be collected and registered on inclusion: age, sex, body mass index (BMI), body temperature, interval between onset of AC and drainage, comorbidities and coexisting conditions, american society of anesthesiologists (ASA) grade, charlson comorbidity index (CCI), AC grade based on TG 18 severity grading,^[4]^ white blood cell (WBC) count, electrolytes, total bilirubin, C-reactive protein (CRP), and so on. This would systematically reflect the characteristics of participants.

The peri-drainage data would be obtained from 2 hours before drainage to one week after ENGBD or PTGBD, such as drainage success, clinical remission, adverse events, pain scores within 2 hours before drainage and at post-drainage 24 h, 48 h, 72 h, etc.

The following data are collected and registered on peri-LC: gallbladder wall thickness changes (pre-drainage to pre-LC), duration and hemorrhage of LC, gallbladder integrity, drainage tube, hospitalization (hospital stay after gallbladder drainage and cholecystectomy), surgical site infection, severe adhesion, pathology, and LC-related complications.

Results that are negative or undetected or measured as 0 should have corresponding symbolic representation and can not be vacant, in order to distinguish from missing values. The treatment of outliers should be judged from both medical and statistical aspects by the statistician during blind examination.

Images and biological samples including venous blood and bile will be collected for probably ancillary and long-term research. Also, all patients will be followed up 6 months after cholecystectomy.

The volunteers of data acquisition have rich clinical experience and rigorous working attitude, and received training and guidance. Data storage would be carried out by two independent investigators to ensure reliability and validity.

We would also pay attention to and collect the information of the participants who discontinue or deviate before cholecystectomy and the follow-up are completed. To promote participants’ retention and enthusiasm, we would establish workflow manuals contact patients regularly, communicate properly and take effective care of their health.

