#### Analysis

2.14.2

A predefined statistical analysis plan will be followed. All statistical analyses were conducted with IBM SPSS (version 21.0). *P* values of <.05 were considered to represent statistical significance. Categorical variables would be reported as counts and percentages. The mean and standard deviation or median with interquartile ranges (IQR) were used to describe continuous variable data, as appropriate.

The primary analysis is a comparison between ENGBD and PTGBD for the pain remission based on an intention-to-treat principle. A multilevel, random-slope model would be fitted to the data with time points nested in patients to allow for clustering of data within each patient. This model adjusted for the fixed effects of treatment group, time (−2, 24, 48 , or 72 hours), and treatment × time interaction. An unstructured covariance pattern was selected for the repeated measurements as the least restrictive structure, which resulted in better model fit based on log-likelihood values than more constrained patterns. Estimates of the difference in pain scores between treatment groups were assessed overall and at individual time points.

The secondary analysis is a comparison between ENGBD and PTGBD for the rates of technical and clinical success, adverse events, and changes in the gallbladder wall thickness . Also, the outcomes during cholecystectomy including time duration, open conversion would also be analyzed. The Chi-square test or Fisher exact test was used for dichotomous variables, and Wilcoxon test was used for rank data. For quantitative data, two-tailed Student *t* test is used, if the normal distribution and homogeneous total variance are satisfying, otherwise, Wilcoxon test is used.

A blinded adjudication committee will assess the occurrence of the primary and secondary endpoints after the last patient has completed follow-up.

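### The statistician is said to be blind to group and to judge outliers blind, yet the statistician also generates the allocation list and no second person is named, so the claimed masking is contradicted and not secured as written

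*Protocol article*

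**What the plan says.** Five places in the protocol article bear on this.

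- Section 2.3 (Trial design) describes a non-blind trial but adds that "the statistician would not know the grouping".
- Section 2.12 (Allocation sequence generation and randomization) states: "The randomization numbers were generated by statistician using computer program with 1:1 allocation, stored and encoded 20 sealed, opaque envelopes independently". At enrolment, "two volunteers first record the name and the code of the next unopened envelope", and they then open it.
- Section 2.13 (Blinding) says patients and physicians are unblinded, but that "the assessor of clinical and biological data in charge of statistical analyses and outcome assessment will be masked as to the subjects assigned group". It also masks the investigator who collects secondary outcomes.
- Section 2.14.1 (Collection, management) states: "The treatment of outliers should be judged from both medical and statistical aspects by the statistician during blind examination".
- Section 2.14.2 (Analysis) states: "A blinded adjudication committee will assess the occurrence of the primary and secondary endpoints after the last patient has completed follow-up".

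The primary outcome (section 2.8.1) is a visual-analogue pain score from 0 to 10. The patient marks it and a trained nurse reads it, before drainage and at 24, 48 and 72 hours after.

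**The concern.** One role word, statistician, covers three tasks: making the allocation list, not knowing the allocation, and deciding blind how outliers are treated. Whoever makes the list and encodes the envelopes knows which code means which arm, and cannot at the same time be the person who does not know the grouping.

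This matters more here than in a double-blind trial. The patient who marks the primary outcome knows which tube is in place, so masked handling of the data is one of the few protections left. The outlier rule is a matter of judgement and the planned sample is 22 patients. If the person judging also holds the list, a report that repeats section 2.3 would claim a blinding that the trial did not have.

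**Working it through.** **1. The passages side by side**

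| Task | Who, according to the article | Section |
|---|---|---|
| Generate the randomization numbers | statistician | 2.12 |
| Encode and store the envelopes | same sentence, no other person named | 2.12 |
| Not know the grouping | the statistician | 2.3 |
| Judge outliers blind | the statistician | 2.14.1 |
| Be in charge of analyses, masked | an assessor | 2.13 |
| Record patient name against envelope code, open the envelope | two volunteers | 2.12 |
| Hold the code-to-arm key | not stated | none |

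The first four rows cannot all be true of one person. They can be true of two people, but the article does not say that there are two.

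**2. Can the list be linked to patients?** The volunteers, not the statistician, write the name against the code. But they take the next unopened envelope, so the envelopes are used in sequence. If the codes follow the list order, enrolment order together with the list gives the arm, without any names. Coding of identities (section 2.19) does not prevent this, and the article does not say that enrolment order is kept from the analyst.

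**3. How far could one decision move a mean?** Inputs from section 2.10: PTGBD mean 5.4, SD 3.1; ENGBD mean 1.3; planned difference 5.4 − 1.3 = 4.1; 11 per arm. I take SD 3.1 for both arms, which reproduces the plan's own figure: n = 2 × [3.1 × (1.960 + 0.842) / 4.1]² = 8.97, so 9 per arm as stated.

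If one score x is deleted from 11 with mean m, the new mean is (11m − x)/10.

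| Arm | Score deleted | New mean | Shift | Share of 4.1 | Effect on the difference |
|---|---|---|---|---|---|
| PTGBD, m = 5.4 | 10 | (59.4 − 10)/10 = 4.94 | 0.46 | 11% | shrinks |
| ENGBD, m = 1.3 | 10 | (14.3 − 10)/10 = 0.43 | 0.87 | 21% | grows |
| ENGBD, m = 1.3 | 5.4 | (14.3 − 5.4)/10 = 0.89 | 0.41 | 10% | grows |

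The third row stands for an ENGBD patient with pain at the PTGBD average. Technical success of ENGBD is given as 88.9% (section 1) and 81% (section 3), which implies 0.111 × 11 = 1.2 to 0.19 × 11 = 2.1 failures in 11. Section 2.7 lists PTGBD among the alternative procedures, and under intention-to-treat these patients stay in the ENGBD arm. If their pain resembles PTGBD pain (an assumption), their scores look ordinary in pooled data and extreme only to someone who knows the arm.

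**4. Would the conclusion change?** A simple t statistic at one time point, with SD held at 3.1 and the planned difference true:

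- nothing deleted: 4.1 / [3.1 × √(1/11 + 1/11)] = 4.1/1.32 = 3.1
- one PTGBD score of 10 deleted: 3.64 / [3.1 × √(1/10 + 1/11)] = 3.64/1.35 = 2.7
- two deleted: mean (59.4 − 20)/9 = 4.38, so 3.08 / [3.1 × √(1/9 + 1/11)] = 3.08/1.39 = 2.2

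The critical value is about 2.1. At the planned effect the result survives, narrowly after two deletions. All of this is illustration at one time point. The primary analysis is a repeated-measures mixed model over four time points, in which one missing score acts differently.

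**The case against.** The strongest reply is that a reader might infer that the masking does not exist, and the article does not go that far. It never says that the list-maker and the analyst are one individual. Section 2.13 gives the analyses to a masked assessor who may be someone else, and the word on independence in section 2.12 could mean a separate role. The list unmasks an analyst only if the data can be linked to code or order, on which the article is silent. Key custody is also often left to the full protocol. This stands against the stronger reading. It does not remove the contradiction, because sections 2.3 and 2.14.1 give blind status and outlier judgement to the statistician, not to the assessor.

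Three further inferences should be resisted.

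- **That section 2.13 masks only the collector of secondary outcomes.** It also masks the assessor in charge of analyses and outcome assessment.
- **That an adjudication committee has nothing to do for the pain score.** Section 2.8.1 sets conditions for a valid score (a conscious, communicating patient, and an analgesic-free interval), and a committee could check these. What it cannot do is undo bias already in the mark.
- **That one outlier decision would reverse the result.** The arithmetic above does not show this. A score of 10 in the PTGBD arm lies only (10 − 5.4)/3.1 = 1.5 SD above the mean, which conventional rules would not flag. Section 2.14.1 speaks of treating outliers in all data, not of deleting pain scores.

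It is also fair to say that the trial has other safeguards: opaque envelopes, a scale with its numbers hidden from the patient, and independent auditing.

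**Conclusion.** The concern holds in a limited form. Sections 2.3, 2.12 and 2.14.1 contradict each other on whether the statistician knows the allocation, and nothing in the article separates the roles. The claimed masking of outlier decisions and analysis is therefore contradicted and not secured as written. Whether the analysis was unmasked in practice cannot be told from the document.

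The possible effect on the result is modest. In the illustrations, deleting one score moves an arm mean by 0.41 to 0.87 points, or 10% to 21% of the planned difference. These figures rest on raw means at one time point, the planning values of section 2.10 and 11 patients per arm. They show why the outlier rule should not depend on judgement; they do not show that the primary conclusion would change. The point should be corrected, but it does not invalidate the design.

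**What to change.** 1. Reconcile sections 2.3, 2.12, 2.13 and 2.14.1. State that the list and the code-to-arm key are held by a person with no role in analysis. This need not be an auditing committee member, since that committee audits the trial's procedures. State that the analyst receives data labelled A/B, without envelope code or enrolment order, until outlier decisions are locked.
2. The list already exists and recruitment has opened. If its maker is also the analyst, say plainly that the statistician is not blind, and remove the opposite claim.
3. In either case, keep every valid 0-10 pain score in the primary analysis and confine any outlier exclusion to a sensitivity analysis. This protects the result even if the list cannot be replaced.
4. State beside the adjudication sentence in section 2.14.2 that blinded adjudication cannot remove bias from a pain score marked by an unblinded patient.

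The cost is one reassigned task or a less favourable statement about blinding, and a few amended sentences. Under section 2.18, a change to the analyses needs ethics committee approval.

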### Participants, interventions, and outcomes

2.4

This manuscript written adheres to SPIRIT 2013 Statement.^[14]^

### Study setting

2.5

The trial would be set at an university affiliated tertiary-care A hospital center, which performs approximately more than 2000 Endoscopic Retrograde Cholangiopancreatography (ERCP) procedures per year. The outline of trial procedures is presented in Figure 1.

**Figure 1 F1:**
[figure not shown]
Flow chart of participants.

### Eligibility criteria

2.6

#### Inclusion criteria

2.6.1

Patients that were not considered suitable for early or urgent cholecystectomy because of high-surgical risk, in which case biliary drainage followed by delayed LC is recommended by the TG18 flowchart: Grade II (moderate) AC, antibiotics and general supportive care fail to control inflammation; Grade III (severe) AC, after antibiotics and general organ support, negative predictive factors present including jaundice (TBIL ≥2), neurological dysfunction, respiratory dysfunction, or no negative predictive factors present but American Society of Anesthesiologists physical status classification (ASA-PS) is 3 or greater or Charlson comorbidity index (CCI) is 4 or greater.

#### Exclusion criteria

2.6.2

Exclusion of patients who meet one or more of the following criteria: age <18 or >90 years, pregnant or breastfeeding, severe obesity (body mass index ≥35 kg/m^2^), consent refusal, coagulation dysfunction (INR > 1.5) and low-peripheral blood platelet count (<50 × 10^9^/L), using anticoagulation or antiplatelet drugs; bile duct stones; prior surgery of Bismuth II, Roux-en-Y and choledochojejunostomy, preoperative coexistent diseases: acute pancreatitis, GI tract hemorrhage or perforation, severe liver disease (such as decompensated liver cirrhosis, liver failure, and so on), any malignant diseases.

#### Endoscopic surgeons criteria

2.6.3

All ERCP operations and LC are completed by an endoscopic surgeons team, with more than 10 years of ERCP and 20 years of LC experience, 400 cases of ERCP and 450 cases of LC per year at present.

### Interventions

2.7

A systematically trained experienced attending physician assesses that once evidence of gallbladder drainage is available, all patients eligible for inclusion were informed fully of written informed consent, then would be randomly assigned to the interventional group (ENGBD) or to the reference group (PTGBD). Of course, risks and benefits associated with surgery would be routinely communicated and agreed in writing.

The experimental group patients are sedated by intravenous administration of sufentanil and propofol, then selective bile duct cannulation, a 0.025- or 0.035-inch guidewire is advanced into the cystic duct and subsequently into the gallbladder, withdraw the catheter, a 5Fr naso-gallbladder catheter is inserted into the gallbladder along the guidewire. PTGBD is guided by ultrasound, an 18-gauge needle is inserted into the gallbladder, a 0.035-inch guidewire is coiled into the gallbladder and a 9Fr dilator expands the skin, then an 8Fr 20 cm catheter is placed.

When ENGBD was technically unsuccessful or clinically ineffective, endoscopic nasobiliary drainage (ENBD), PTGBD and EUS-GBD were used as alternative procedures. The patients of inclusion would be given appropriate and quality treatment at anytime, in order to reduce waiting and improve adherence. Properly trained volunteers would accompany patients on key treatments, such as ERCP and PTGBD, extubation, LC, etc. This not only improves adherence, because of the convenience to patients, but also monitors adherence to a certain extent.

All patients of inclusion would be assessed by the attending physician in accordance with recent guidelines for AC management, including sufficient infusion, maintenance of electrolyte balance, antibacterial agents, the monitoring of respiratory and hemodynamics, correction of acidosis and complications.

In particular, there is no strict recommendation for extubation time, ENGBD group would extubate when the bile in the naso-gallbladder tube becomes clear, which is approximately 4 days after the drainage based on our experience. PTGBD group extubate after more than 2 weeks due to fistula formation. Also, no consensus has been reached about the optimal timing of LC after drainage. Because most studies^[15–17]^ figure out the short interval increases intraoperative difficulty, we require all patients to undergo cholecystectomy 3 months after drainage, so that edema and inflammation around the gallbladder subsided completely.

### Outcome

2.8

#### Primary outcome measures

2.8.1

The primary outcome is the pain score, defined as pain experienced during mobilization from the supine to the standing position. Using the visual-analogue scale, pain score would be obtained within 2 hours before drainage and at post-drainage 24, 48, and 72 hours in conscious and communicating patients by a specially trained nurse, who devoted herself to the objectivity and authenticity of the scores. The details of assessment are as follows: draw a 10-cm line on a piece of paper, mark one end of the line with the number 0, indicating no pain; the other end with 10, indicating the most severe pain; the middle part indicates different degrees of pain. While assessing the pain of patients, make sure the patient could not see the numbers on the paper and let them mark the position according to their feelings about the pain. Then the nurse would get a score based on the mark. Pain scores reflect directly the degree of pain, the remission of pain not only relieves the pain symptoms associated with acute cholecystitis itself, but also relatively alleviates the severe pain caused by tube.

In order to avoid the effects of anesthesia, we chose to evaluate the pain 24 hours after drainage. Especially, all pain assessments should be performed without the administration of pain killers or after using an analgesics for 6 hours. All modifications in pain management are recorded. Our team routinely prepares a multimodal approach to pain management, which is applied mainly based on nonsteroidal anti-inflammatory drugs and other adjuvant drugs, but tries to avoid applying it.

